## Abstract

**Background:**

Idiopathic scoliosis is the most common spinal deformity in children. Treatment strategies aim to halt progression of the curve. Mild scoliosis is in many cases observed or, in some cases, treated with scoliosis-specific exercises. More severe curves are treated mainly with a brace. The aim of this study is to investigate the effectiveness of scoliosis-specific exercises compared to observation in adolescents with mild idiopathic scoliosis.

**Methods:**

**Subjects**. Previously untreated and skeletally immature children aged 9–15 years of age with idiopathic scoliosis (curve magnitude Cobb 15–24 degrees) will be included. A total of 90 subjects will be included to receive one of two possible interventions.

**Interventions**. Both groups will receive a physical activity prescription according to the World Health Organization recommendations. The intervention group will receive an additional active self-correction treatment strategy for curve correction and will have outpatient sessions once every two weeks for the first three months. They will be prescribed to do the exercises at least three times per week. The intervention will be performed until skeletal maturity or progression of the curve.

**Outcome**. The subjects will participate in the study until curve progression or until skeletal maturity (defined as less than 1 cm growth for six months). The primary outcome variable is failure of treatment, defined as progression of the Cobb angle more than 6 degrees on two consecutive x-rays compared to the baseline x-ray. Secondary outcome measures include patient-reported outcomes, clinical characteristics (i.e. angle of trunk rotation and trunk asymmetry) and number requiring brace treatment. Clinical follow-ups will be performed every six months and radiographs will be taken annually.

**Discussion:**

This study will compare effectiveness of an active self-corrective exercise strategy in mild idiopathic scoliosis with observation in terms of halting curve progression.

## Background

Idiopathic scoliosis is the most common spinal deformity in children and adolescents with an estimated prevalence of 3% [1]. About one tenth of the children with scoliosis develop a deformity that requires treatment with brace or surgery with the current treatment protocol. In the Swedish health care system, school screening programs account for at least 200,000 children screened for scoliosis per year. Children with a suspected scoliosis are usually referred to orthopedic specialists for evaluation. If a mild scoliosis exists, clinical observation during growth is the mainstay in Sweden. If progression occurs and the scoliosis requires treatment (Cobb ≥ 25 degrees), standard treatment in Sweden consists of bracing. The gold standard in treatment is a rigid thoracolumbosacral (TLSO) brace worn 18–20 hours or more per day, aiming to halt curve progression, although night-time brace is an alternative [2]. Previous literature on quality of life has suggested that brace treatment, being in many cases tough and cumbersome on adolescents, might have negative effects on mental health and studies have also shown that patients surgically treated for idiopathic scoliosis are to a larger extent satisfied with management [3–5].

Scoliosis specific exercises have in previous studies shown possible benefits in mild scoliosis curves and may be used as a method to prevent brace treatment, but the findings are not generally accepted [6–8]. The International Scientific Society on Scoliosis and Rehabilitation Treatment (SOSORT) recommends scoliosis-specific exercises (SSE) to be the first line of treatment in mild scoliosis to halt curve progression [9]. A recent review of SSE concluded that insufficient evidence exists supporting SSE in terms of improving scoliotic curves and warranted further high-quality evidence [10]. Furthermore, the lack of evaluation and follow-up until skeletal maturity [11] and comparison of scoliosis specific exercises with observation alone in mild scoliosis make valid conclusions difficult to draw [6]. Therefore, there is a need of a randomized controlled trial addressing these issues to determine the effectiveness of SSE for idiopathic scoliosis.

In a multicenter randomized trial, we aim to investigate the effectiveness of an active self-correction rehabilitation strategy with observation in adolescents with mild idiopathic scoliosis.

## The question at issue/hypothesis

We hypothesize that:

-Scoliosis specific exercises reduce the number of adolescents with scoliosis progression of more than 6 degrees, measured according to Cobb [12], on a standing frontal radiograph with a primary curve equal to or greater than 25 degrees compared to observation alone.

## Methods

### Study design

This study is a prospective randomized controlled trial. The protocol has been registered on ClinicalTrials.gov, identifier: NCT05138393. Currently, this project will be performed on two sites: Karolinska university hospital in Stockholm and Linköping university hospital in Linköping, Sweden. Further centers may be involved continuously. Individuals that meet inclusion criteria will be asked for participation. After informed consent, randomization will take place.

### Subjects

Patients referred to the participating clinics are consulted and examined by a health-care provider specialized in spinal disorders. The magnitude of the scoliosis in the frontal plane is assessed by measuring the Cobb angle [12]. Upon inclusion, full spine frontal and sagittal radiographs, pelvic and hand radiographs will be taken. Up to three months old radiographs will be accepted. Fig 1 illustrates the flow process for included patients and Fig 2 illustrates the recruitment process. The following inclusion criteria will be applied:

Skeletally immature patients. Sander’s score ≤ 4 [13], Risser sign < 2 and no menarche for females.Age 9–15 years of age at inclusion.Primary curve of 15–24°.Apex of the primary curve at T7 or caudalScoliosis of idiopathic nature (i.e. no neuromuscular, congenital or syndromic origin).

**Fig 1 pone.0285246.g001:**
[figure not shown]
SPIRIT schedule of enrollment.

**Fig 2 pone.0285246.g002:**
[figure not shown]
Flow scheme of recruitment process.

## Interventions

### Scoliosis specific exercises

The treatment will aim to teach the patients to become proficient in performing active self-correction of their scoliosis in the sagittal, coronal and horizontal planes. An additional step is combining the self-correction techniques in three dimensions (auto-correction in 3D) and stabilizing the corrected posture in accordance with SOSORT guidelines [9]. Patients will also be informed and educated in self-corrective behavior during task-oriented activities in daily living in order to enhance neuromotor control of the spine and limbs. Patients will have outpatient sessions once every two weeks the first 3 months and perform the exercises at home in 30-minutes sessions at least three times per week. Additional single bolus outpatient sessions may occur when extra education is required to master the program. Reinforcement of the intervention will be performed in conjunction with outpatient reassessment every six months. Patients are encouraged to continue with non-specific self-mediated physical activities of moderate intensity at least 60 minutes daily, for the entirety of the study. Compliance to the home exercise program will be monitored by using a mobile application (Physitrack, www.physitrack.com) where the patients record their sessions and can have contact with the research personnel. More detailed description of the scoliosis specific exercise intervention is provided in supplementary S1–S3 Files.

The head physiotherapists have a long and vast experience in managing and treating idiopathic scoliosis patients, both from a clinical and scientific perspective (together approximately 20 years of experience).

### Observational group (non-specific activity only)

Patients are encouraged to continue with non-specific self-mediated physical activities of moderate intensity at least 60 minutes daily, for the entirety of the study. If needed, the patients might be offered one outpatient session (remote or at the hospital) for information on self-mediated physical activity. Reinforcement of the intervention will be performed in conjunction with reassessment every six months.

### Non-participants

Patients not willing to undergo randomization will be treated in accordance with local procedures. Observation will be offered during growth and in the case of deterioration with a curve reaching at least 25 degrees in Cobb angle with remaining growth, fulltime TLSO brace treatment or night-time brace will be offered. The radiological and clinical result of these patients will be obtained from the regular orthopaedic files and radiographs taken.

### End of study

The study will be terminated when the participant reaches skeletal maturity, defined as less than 1.0 cm growth of body height in six months, or if the curve progresses more than 6 degrees, compared to the baseline radiograph, seen on two consecutive spinal standing radiographs. In case of curve progression and a Cobb angle surpassing 25 degrees, treatment will be offered with standard TLSO or nighttime brace to be worn 20 hours and 8 hours, respectively, per day. In the event that a Cobb angle surpasses 45 degrees with risk for further progression, patients will be offered surgical treatment. Follow-ups will be done in similar way also for those failing treatment. Post-treatment follow-up after endpoint is planned to occur at 2, 5 and 10 years prospectively including full spinal frontal and sagittal radiographs.

### Ethical permit

This study has been ethically approved by the Swedish Ethical Review Authority (approved 2021-04-20. Diary number: 2020–06502 and 2021–04632).

### Randomization procedure

After assessment, patients fulfilling the inclusion and exclusion criteria will be asked to give written and signed consent for participation. If the patient is aged less than 15 years, parental consent is also required. Patients who decline participation will be monitored as part of clinical routine.

Randomization will be done in a 1:1 ratio. Randomization will be performed using an online module available through the Swedish spine register (www.swespine.se). Randomization sequence have been prepared by an independent data manager at MedScinet (www.medscinet.com), the company that runs the register platform, and is unknown to the researchers.

### Blinding

Blinding of patients and clinicians is not possible. The statistician assessing the outcome will also be blinded to the type of treatment participants have had. In case of suspected progression during each follow-up including radiographs, two experts blinded for type of treatment will assess the radiographs to determine if progression has occurred.

### Outcome measurements

Primary outcome measure is progression of more than 6 degrees in Cobb angle seen on two consecutive radiographs from baseline and during radiographic follow-ups. Radiographs (hand and standing full-spine frontal and sagittal) will be taken every twelve months and clinical follow-ups will be performed every six months until skeletal maturity. The endpoint failure of treatment is defined as an increase of the Cobb angle of more than 6° from the time of the first radiograph on two consecutive examinations, considered as the minimal clinically important difference [14]. If progression is suspected, additional radiographs may be taken for verification, also at additional time points not being considered as regular follow-ups. The number of patients progressing to a curve requiring brace treatment will be recorded and compared in both groups. Indication for brace treatment is progression of more than 6 degrees together with a primary curve ≥ 25 degrees and remaining growth.

Secondary outcome measures recorded at baseline and every six months for the entirety of the study include angle of trunk rotation, as measured with Bunnell’s scoliometer [15], SRS-22r and EQ-5D-Y quality of life questionnaires, VAS-pain, the International Physical Activity Questionnaire (IPAQ-SF) short form, Spinal Appearance Questionnaire (SAQ) and number requiring brace treatment.

In line with the capability, opportunity, motivation, and behaviour change model (COM-B) [16], to gain knowledge of behavioural outcomes, all study participants will answer three additional questions during each six-month follow-up; 1) the grade to which you feel that you have completed the treatment (adherence), 2) the grade to which you are motivated to carry out the treatment (motivation) and 3) how confident are you in your own capability to perform the treatment (capability). Additionally, the healthcare provider answers the question “to what grade the patient has adhered to treatment plan” (patient adherence). These questions are rated on a scale from best “very sure” (1 point) to worst “not at all” (4 points).

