### Data analysis

Data from the trial will be compared based on the ’intention to treat’ principle. An intention to treat (ITT) analysis means that all patients, regardless of non-compliance, loss to follow-up or drop-out, remain in the analysis of the group to which they were randomized [17]. Depending on the mechanisms for missing data, the most relevant imputation method considering missing at random or not missing at random will be used in the ITT analysis [18]. A causal survival analysis measuring complier average causal effects (CACE), where standardization of baseline covariates (age, sex, Risser sign, major curve) and inverse probability weighting of post-randomization treatment adherence data is used in a per protocol analysis, to be contrasted with ITT results [19]. With basis in the COM-B model, patient reported capability and motivation can be hypothesized as potential mediators of treatment effect on the outcome variables. Fig 3 summarizes these causal inferences in a direct acyclic graph (DAG) model [20]. If a patient fails treatment and is offered another treatment, such as brace or surgery, the Cobb angle at the moment of commencing this treatment will be considered in the secondary outcome analysis of Cobb angle. Categorical parameters will be compared by the Chi-square test. Continuous and discrete parameters will be measured using parametric or non-parametric tests (depending on skewness) for group comparisons. Individual variables will be tested for their association with treatment effect by adding a predictor × treatment group interaction term to a regression equation. Additionally, Kaplan-Meier survival analyses will be used to display the probability of more than 6° Cobb progression over time. Cox regression or pooled logistic regression will be used to provide survival hazard ratios. The results will be reported according to Consolidated Standards of Reporting Trials (CONSORT) [21].

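### Motivation, capability and possibly adherence can be rated after progression is already suspected, which exposes the mediation and per-protocol analyses to reverse causation

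*Protocol article*

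**What the plan says.** All places are in the Methods of the Protocol article.

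- **Outcome measurements.** "all study participants will answer three additional questions during each six-month follow-up": self-rated adherence, motivation and capability, each on a four-point scale. "Additionally, the healthcare provider answers the question" on how well the patient has adhered.
- **Outcome measurements, schedule.** Radiographs "will be taken every twelve months and clinical follow-ups will be performed every six months until skeletal maturity". "If progression is suspected, additional radiographs may be taken for verification", also outside the regular visits. Failure is more than 6 degrees over baseline on two consecutive examinations.
- **Blinding.** "Blinding of patients and clinicians is not possible". The statistician is blinded, and where progression is suspected "two experts blinded for type of treatment will assess the radiographs to determine if progression has occurred".
- **Data analysis.** The main comparison is by intention to treat. To contrast with it, "inverse probability weighting of post-randomization treatment adherence data is used in a per protocol analysis", aimed at a complier average causal effect. Patient-reported capability and motivation are put forward as potential mediators, and the Fig 3 caption defines a path from mediator to outcome.
- **Scoliosis specific exercises.** Patients log their home sessions in a mobile application. Data analysis does not say whether this log or the visit ratings supply the adherence data.

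**The concern.** A mediator, or a measure of treatment received, has to precede the outcome it is meant to explain. Here the ratings and the films share one visit series, the raters know the treatment, and the text does not put the rating ahead of the film result. A child who has learned that the curve has grown may report less motivation and confidence. A provider who knows it may grade past adherence lower.

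The two-film rule adds to this, because the formal failure date can come well after progression was first seen. A rating dated before failure may still be a response to it. At stake are the mediation analysis, where motivation and capability have no other source than these ratings, and the weighted per-protocol analysis to the extent that it uses them.

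**Working it through.** **1. Order in time.** The plan gives no figure for these analyses, so the first check is the schedule. Take a child whose first film over 6 degrees is at month 12 and whose confirmation waits for the next annual film.

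| Visit | Scheduled film | Position of the rating |
|---|---|---|
| Month 6 | no | before the first film over 6 degrees |
| Month 12 | yes, over 6 degrees | before or after, depending on the order within the visit |
| Month 18 | no | after the first film, before confirmed failure |
| Month 24 | yes, confirms | after the first film |

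Up to three ratings (months 12, 18 and 24) can follow seen progression. A cut at the confirmed failure date would keep month 18, so the cut has to be at the first film. If an unscheduled film confirms progression soon after month 12, only the month-12 rating is in question, and none is if it was given before the film. The range is therefore zero to three per failing child.

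**2. Number of children who could be affected.** From Power analysis (45 per group; 39% and 10% failure): 0.39 × 45 = 17.6 in observation and 0.10 × 45 = 4.5 in exercise. These are expected failures, which is an upper limit on failing children with an affected rating.

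**3. Spurious link between rating and outcome.** Assumptions not in the documents: the rating has no true effect, a share b truly rates high, and a share q of high-rating children who fail is downgraded. The rating that enters the analysis is one made after progression was seen. With failure rate f:

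- risk if rated high = f·b(1−q) / [f·b(1−q) + (1−f)·b]
- risk if rated low = f·[1−b(1−q)] / {1 − [f·b(1−q) + (1−f)·b]}

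For f = 0.10, b = 0.7, q = 0.2: 0.056/0.686 = 0.082 and 0.044/0.314 = 0.140, a risk ratio of 0.58.
For f = 0.39, same b and q: 0.2184/0.6454 = 0.338 and 0.1716/0.3546 = 0.484, a risk ratio of 0.70.

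| q (b = 0.7) | Risk ratio, f = 0.10 | Risk ratio, f = 0.39 |
|---|---|---|
| 0 | 1.00 | 1.00 |
| 0.1 | 0.75 | 0.83 |
| 0.2 | 0.58 | 0.70 |
| 0.5 | 0.27 | 0.42 |

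At f = 0.10 and q = 0.2, moving b from 0.6 to 0.8 gives 0.65 to 0.49.

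**4. Consequence for mediation.** Under the same assumptions the share rated high is 0.686 in exercise and 0.645 in observation. The difference is b·q·(0.39 − 0.10) = 0.7 × 0.2 × 0.29 = 0.041, although exercise does nothing to the mediator. The intervention-to-mediator and mediator-to-outcome paths both become non-zero, so an indirect effect can appear where none exists.

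**5. Direction in the per-protocol analysis.** As a simplified stand-in for the weighted analysis, let all children truly adhere and exclude those rated non-adherent, with q = 0.2.

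| Downgrading acts in | Exercise risk | Observation risk | Risk difference | Risk ratio | Odds ratio |
|---|---|---|---|---|---|
| neither arm | 0.100 | 0.390 | 0.290 | 0.256 | 0.174 |
| both arms | 0.08/0.98 = 0.082 | 0.312/0.922 = 0.338 | 0.257 | 0.241 | 0.174 |
| exercise only | 0.082 | 0.390 | 0.308 | 0.209 | 0.139 |

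Applied to both arms, the risk difference shrinks, the odds ratio does not move and the risk ratio moves slightly. Applied to the exercise arm alone, the effect is exaggerated on all three scales.

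**The case against.** The best reply is that this is mostly an absence. A condensed article need not print the order of forms and films within a visit, and a lag belongs in the statistical analysis plan. Nothing states that ratings follow disclosure of the film or that late ratings will be used. This stands in part: an analysis plan could set the lag. It could not restore the order within a visit once ratings have been given after the result was known. The design that allows this, with unblinded raters, shared visits and a two-film endpoint, is stated in the article.

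A reader might infer four stronger things, none of which the documents support.

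- *That the measured exercise dose is contaminated.* Data analysis names no source for adherence and never ties the provider's grade to the weights. The app log is a separate record that need not follow the film result. It is, however, patient-entered, described only for the home exercise programme, and silent on motivation and capability.
- *That the per-protocol effect must be exaggerated.* Step 5 shows that this needs the adherence selection to act mainly in the exercise arm.
- *That 39% and 10% of the arms carry contaminated ratings.* Those are expected failures. Early confirmation on an unscheduled film, or a rating given before the film, leaves no affected rating before confirmation.
- *That the trial's main result is at risk.* The intention-to-treat comparison does not use the ratings, and suspected progression is judged by blinded experts. The bias runs from outcome to rating.

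The mediation plan is also worded tentatively, and month-6 ratings precede the first scheduled follow-up film and remain usable.

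**Conclusion.** The point holds for the secondary analyses only. Motivation and capability have a single source, the unblinded child at follow-up visits, and such a rating can come after progression is suspected but before failure is confirmed. The same applies to adherence if the visit ratings are what the weighted per-protocol analysis uses.

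The size cannot be fixed from the documents, because the share of true high raters and the rate of downgrading are assumed. With 70% rating high and 10% to 50% downgraded, the spurious risk ratio runs from 0.75 to 0.27 at 10% failure and from 0.83 to 0.42 at 39%. These figures also assume that a post-film rating is used for every failing child, so they are upper-end illustrations. The direction of the per-protocol bias is open until the plan says which arms adherence is applied to. The intention-to-treat result and the sample size are unaffected.

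**What to change.** **Outcome measurements:** have the child and the provider complete their ratings before that visit's radiograph is taken or its result disclosed.

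**Data analysis:** use only mediator and adherence ratings that precede the first film showing more than 6 degrees, not the confirmed failure date, and keep later ratings for a sensitivity analysis. Name the adherence source. For the exercise arm, use app sessions logged before that film. State in which arms adherence is applied.

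**Cost:** the order of procedures at an existing visit and a few sentences of text. In a failing child up to three ratings may be discarded before confirmation (months 12, 18 and 24 in the example; two if the month-12 rating was given before the film). Two limits remain: the six-monthly scoliometer reading can still signal progression before a rating is given, and the app log is self-entered.

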**Fig 3 pone.0285246.g003:**
[figure not shown]
Directed acyclic graph of hypothesized mechanisms in single mediator models in the PREMISCOPRO trial and the estimated averaged effects standardized for baseline covariates and inverse probability weighted for post-randomization treatment adherence confounding. The indirect effect (*ab*-product) is the average intervention effect through the mediator. *a*, a-path (the intervention-mediator effect); *b*, b-path (the mediator-outcome effect); *c*, c-path (the total effect of the intervention on the outcome, without accounting for potential mediator); c′ (the direct effect of the intervention on the outcome, that works through all other mechanisms excluding the selected potential mediator).

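### The mediator items ask about 'the treatment', which differs by arm, so the intervention-to-mediator path mixes a change in capability or motivation with a difference in the task rated

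*Protocol article*

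**What the plan says.** All of this is in the protocol article.

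- **Items.** Under Outcome measurements, the motivation item asks "the grade to which you are motivated to carry out the treatment (motivation") and the capability item asks "how confident are you in your own capability to perform the treatment (capability").
- **Who and when.** "all study participants will answer three additional questions during each six-month follow-up".
- **Scale.** "These questions are rated on a scale from best “very sure” (1 point) to worst “not at all” (4 points").
- **Use.** Under Data analysis, "patient reported capability and motivation can be hypothesized as potential mediators of treatment effect on the outcome variables". The Fig 3 caption defines the "a-path (the intervention-mediator effect") and takes the ab-product as the indirect effect.
- **Exercise arm.** Scoliosis specific exercises describes taught active self-correction in three planes and then combined in 3D. There are outpatient sessions every two weeks for three months and 30-minute home sessions at least three times a week. The same daily activity advice as in the other arm is added.
- **Observation arm.** "Patients are encouraged to continue with non-specific self-mediated physical activities of moderate intensity at least 60 minutes daily", with one information session offered if needed.

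The article does not say what the word *treatment* in the items refers to in either arm.

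**The concern.** The a-path is a between-arm contrast on a self-rating. Such a contrast has a clear meaning only if both arms rate the same thing. Here allocation may change the child's capability or motivation, and it also changes the task that the child is asked about.

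A control child can truthfully give the top answer about everyday activity. A well-taught exercise child may be less sure about 3D self-correction. The Discussion expects adolescents who can actively manage their scoliosis to gain in capability and motivation. That expectation could be true while the a-path comes out at zero or in the wrong direction. Equally, an a-path could appear where nothing changed except the task.

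What is at stake is the reading of the mediation analysis: whether the trial can say that exercise works, or fails to work, through capability and motivation. The item wording is fixed when the data are collected, so a later analysis plan cannot repair it.

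**Working it through.** **1. Is there a figure to reproduce?** The protocol gives none for the mediation analysis. The only figures borrowed below are the 45 per group and the dropout of up to 20% from Power analysis. The 45 is sized for the primary endpoint. With 10% versus 39%, two-sided 5% and 80% power, the unpooled normal formula gives (1.960 + 0.842)² × (0.10 × 0.90 + 0.39 × 0.61) / 0.29² = 30.6, so 31. Then 31 / 0.80 = 38.75, so 39, and 39 + 5 = 44, close to the stated 45. This has no bearing on the point itself.

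**2. What could *the treatment* mean to the child?**

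| Reading | Object rated, exercise arm | Object rated, observation arm | Consequence |
|---|---|---|---|
| Whole assigned programme | Self-correction plus activity | Activity only | Objects overlap but differ |
| What is specific to the arm | Self-correction | Activity | Objects differ |
| Only the shared activity advice | Activity | Activity | Objects match, but the item misses the skill that distinguishes the arms |
| Each child decides | Varies from child to child | Activity | Objects differ between and within arms |

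None of these readings gives a comparable score that also captures the skill taught.

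**3. What does the a-path estimate?** Reverse the score so that higher is better. Let *a\** be the true effect of allocation on capability or motivation, and *d* the shift that arises only because the exercise arm rates a different task. Then

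measured a = a\* + d, and measured ab = (a\* + d) × b.

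Each item yields one between-arm difference, and that difference contains two unknowns. No model fitted to these data separates them without an outside assumption about *d*. The b-path also pools confidence in different behaviours across the arms.

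**4. Illustration on assumed values (the protocol gives none).**

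- a\* = 0.5, d = −0.5: measured a = 0 (null although the effect is real).
- a\* = 0.5, d = −1.0: measured a = −0.5 (reversed).
- a\* = 0, d = ±0.5: measured a = ±0.5 (spurious).

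**5. Could a purely task-related difference be taken for an effect?** Take 45 × 0.80 = 36 per arm, a two-sided 5% test, the normal approximation and an assumed SD of 0.7 to 1.1. The chance of significance is Φ(|d| / (SD × √(2/36)) − 1.96), ignoring the negligible opposite tail.

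| Assumed difference due to task only | SD 0.7 | SD 0.9 | SD 1.1 |
|---|---|---|---|
| 0.25 point | 33% | 22% | 16% |
| 0.50 point | 86% | 65% | 49% |

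For example, with d = 0.5 and SD 0.7, 0.5 / (0.7 × 0.2357) = 3.03, and Φ(3.03 − 1.96) is about 86%. These rows show what would follow from a shift of that size. They are not evidence that such a shift exists.

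**6. The baseline question.** The listed secondary outcomes are taken at baseline as well: "Secondary outcome measures recorded at baseline and every six months for the entirety of the study include angle of trunk rotation". For the three added questions the text names only the six-month follow-ups. The baseline covariates named under Data analysis are age, sex, Risser sign and major curve, with no prior motivation or capability. Randomization balances prior levels in expectation, so the a-path does not need a baseline value to be unbiased on that account. The b-path is not randomized, and prior motivation may influence both the later score and the outcome. A baseline value would help there.

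**The case against.** The strongest case on the other side has five parts.

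- **The analysis is exploratory.** The aim and the hypothesis concern curve progression only, and mediation is introduced as something that can be hypothesized. This stands. The primary endpoint, the sample size and the intention-to-treat comparison do not use these two items.
- **The arms overlap.** Exercise children receive the same activity advice, so it would be wrong to say that the arms rate wholly separate things. This stands too, but an overlapping object is still not the same object.
- **The article may paraphrase the items.** The questionnaire and its instructions are not shown. That is fair, but both items as printed refer to the treatment, and nothing in the text gives them a common object.
- **The size is assumed.** This stands. A reader might infer that the mediation question cannot be answered at all, or that the a-path will be reversed. The documents support neither. They show that two components are mixed, not how large the unwanted one is.
- **A common referent is not neutral either**, because only one arm is taught self-correction in daily living. This does not stand. If both arms rate the same object, an effect of the teaching on that rating is what the a-path is meant to capture.

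A reader might also infer that the missing baseline is an established fault, or that it causes the problem. The text names follow-up visits only, but the enrolment schedule in Fig 1 is not shown, so absence at baseline is not proven. A question about carrying out a treatment not yet begun could hardly be asked as now worded. A missing baseline also does not make the arms' scores refer to different tasks.

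**Conclusion.** The point holds for the mediation analysis. As worded, the two mediator items attach to different content by arm, so the a-path and the ab-product combine a change in capability or motivation with a difference in the task rated. The result could be null, reversed or spurious.

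The conclusion rests on the printed item wording and the two intervention descriptions. It assumes that children answer about the programme they were given. If they all answered about the shared activity alone, the scores would be comparable but would miss the self-correction skill. The magnitude cannot be derived from the document, and the figures above are conditional on assumed shifts and SDs. The baseline issue is secondary and concerns the b-path. This is a worthwhile, inexpensive improvement to a secondary analysis, not a threat to the trial's main conclusion.

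**What to change.** Add two short items, one on motivation and one on confidence, with a single referent that means the same in both arms, for example managing my scoliosis. Ask them at the existing six-month visits. Also ask them before randomization, if the schedule in Fig 1 does not already provide for such items, so that prior levels can be adjusted for in the b-path. Name these as the mediators. Keep the present items, which ask about the assigned treatment, for describing adherence within each arm.

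The cost is two extra questions at visits that already take place. Children already enrolled will lack the new baseline values and would have to be left out of, or imputed in, the baseline-adjusted mediation analysis. If enrolment is too far advanced for the new items to be useful, report the a-path on the present items with a plain statement that the scores are not comparable between arms, and do not interpret the ab-product as an indirect effect.
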